#### Competing event of death

To determine whether the primary result is robust when the competing event of death is considered (which may influence serum creatinine measurements after surgery), we will also examine a composite outcome of acute kidney injury or death within 5 days of surgery.

#### Alternative definitions of acute kidney injury

We will repeat the primary analysis using alternative definitions of perioperative acute kidney injury including staging definitions,^20,37,38^ and assess the consistency of effect across stages of acute kidney injury based on visual inspection of point estimates and 95% confidence intervals. Despite the large sample size, these supplementary analyses for severe stages of acute kidney injury will have limited statistical power for small effects.

## Recognized Limitations

The primary outcome in this kidney substudy of TRICS-III is perioperative acute kidney injury (defined as an acute rise in serum creatinine concentration from preoperative values).^20^ While virtually all prevention trials of acute kidney injury follow this definition, this outcome is a surrogate endpoint that may not directly impact how a patient feels, functions, or survives. Detailed information on long-term permanent kidney function after hospital discharge will not be available in this trial. Nonetheless, our primary outcome follows the current recommended standard of diagnosis of acute kidney injury.^20^ We will also examine whether intervention effects are consistent across stages of acute kidney injury; despite being less frequent, events of Kidney Disease: Improving Global Outcomes (KDIGO) stage 2 and stage 3 acute kidney injury are more relevant to patients and health care providers. Although it is not possible to blind patients or providers to the intervention allocation, any resulting ascertainment bias should be minimal as we have the same prespecified serum creatinine measurement schedule for patients in both groups. Furthermore, our outcomes will be objectively measured by laboratory technicians unaware of group allocation.

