### Data Collection and Outcomes

Preoperative serum creatinine was obtained within the 30-day period before surgery, where the most recent value before surgery will serve as the baseline value. Participating sites received study funds to measure the postoperative serum creatinine on days 1, 2, 3, and 5 after surgery. To our knowledge, at participating sites, serum creatinine measurements were traceable to isotope dilution mass spectrometry. No urine output data will be used in the primary analysis of this substudy given difficulties with accurately measuring this variable outside of the intensive care unit.

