The primary outcome of the TRICS-III kidney substudy is perioperative acute kidney injury, defined as an acute rise in serum creatinine from the preoperative baseline value, where an acute rise is defined as ≥26.5 μmol/L in the first 48 hours after surgery or ≥50% in the first 7 days after surgery.^20^ Results from an earlier cardiac study with similar enrollment criteria as TRICS-III suggests that our data collection schedule will capture most perioperative acute kidney injury events in the first 5 days of surgery; in this previously published prospective surgery study of 1219 cardiac patients, 15% of patients developed perioperative acute kidney injury (as per our definition); 13.9% of events were observed in the hours following surgery and 38.7%, 38.7%, and 8.7% of events were observed on postoperative days 1, 2 and 3, respectively.^21^ For this reason, our protocol provides each center funding for serum creatinine measures on days 1, 2, 3, and 5 to encourage measurement on these days in all patients; as well, any other serum creatinine measures obtained in the perioperative period as part of routine care are recorded in the trial database (recording both their value and their date). We will compare the number of serum creatinine measurements (and the postoperative days of these measurements) in each intervention group during the hospital stay to examine the potential for ascertainment bias. While health care providers in TRICS-III are aware of the intervention received, this was also the case in our analyses of acute kidney injury within a large randomized trial where coronary artery bypass surgery was done with and without a bypass pump (where there was no difference in the frequency of serum creatinine measurement between the 2 groups given how ubiquitous serum creatinine measurements are in routine care in the perioperative setting^19^). We expect that less than 2% of patients will be missing serum creatinine values in the first 2 days of surgery as a result of death.

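### The shared creatinine schedule does not by itself justify expecting minimal ascertainment bias, because extra draws ordered by unblinded staff probably also count toward acute kidney injury

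*Protocol article*

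**What the plan says.** All references are to the Protocol article.

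- **Outcome** (Data Collection and Outcomes): "an acute rise is defined as ≥26.5 μmol/L in the first 48 hours after surgery or ≥50% in the first 7 days after surgery", measured from the preoperative baseline.
- **Schedule** (same section): "Participating sites received study funds to measure the postoperative serum creatinine on days 1, 2, 3, and 5 after surgery". The stated purpose of the funding is "to encourage measurement on these days in all patients".
- **Other values** (same section): "any other serum creatinine measures obtained in the perioperative period as part of routine care are recorded in the trial database", each with its value and date.
- **Blinding** (same section): "While health care providers in TRICS-III are aware of the intervention received", the earlier trial of bypass surgery with and without a pump is offered as a parallel; it found no difference in measurement frequency between its arms.
- **Planned check** (same section): the number and the postoperative days of creatinine measurements will be compared between arms.
- **Conclusion drawn** (Recognized Limitations): "any resulting ascertainment bias should be minimal as we have the same prespecified serum creatinine measurement schedule for patients in both groups". The only further support given there is that laboratory staff do not know the allocation.

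**The concern.** The outcome is met if any eligible value crosses a threshold, so the chance of meeting it rises with the number of draws. The reason given for expecting little bias, a common schedule, applies only to the scheduled draws. Nothing in the outcome definition limits it to those draws, and the others are requested by clinicians who know the arm. Blinded laboratory staff protect the assay, not the decision to take blood.

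In a noninferiority comparison the direction matters. More testing in the liberal arm would raise its observed rate and favour noninferiority; more testing in the restrictive arm would work against it. The planned comparison of counts and days can show that testing differed. It cannot show whether the conclusion depends on that difference. None of the analyses listed under Other prespecified analyses (complete-case, inverse probability weighted, intention-to-treat, adjusted, composite with death, alternative definitions) is described as limited to scheduled values.

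**Working it through.** The plan gives no figure for ascertainment bias, so there is none to reproduce. The check has four steps.

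**1. Outcome window against schedule.** Timing shares are those the article quotes from an earlier cohort of 1219 patients, 15% of whom had acute kidney injury under the same definition.

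| Postoperative day | Funded draw | Criterion in force | Share of cohort events |
|---|---|---|---|
| 0 (hours after surgery) | no | 26.5 μmol/L or 50% | 13.9% |
| 1 | yes | 26.5 μmol/L or 50% | 38.7% |
| 2 | yes | 26.5 μmol/L (to 48 h) or 50% | 38.7% |
| 3 | yes | 50% | 8.7% |
| 4 | no | 50% | none listed |
| 5 | yes | 50% | none listed |
| 6 and 7 | no | 50% | none listed |

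Sum: 13.9 + 38.7 + 38.7 + 8.7 = 100.0%. Every listed event was seen by day 3. The unscheduled late days therefore carry little weight. What matters is day 0 and second or third draws on days 1 and 2.

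**2. Room for error.** Inputs from Statistical Power: margin 3.5 points, baseline rate 15%, projected 4074 patients (2037 per arm). The interval is the normal approximation named under Statistical Analysis.

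- Half-width = 1.96 × √(2 × 0.15 × 0.85 / 2037) = 2.19 points.
- Largest observed difference that still gives noninferiority = 3.5 − 2.19 = 1.31 points.

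**3. Illustrative simulation, no true difference.** The assumptions, none of them from the article, are about 12 to 15% acute kidney injury on scheduled days, 5 to 7% within-person noise, possible extra draws on days 1, 2, 4, 6 and 7, and a chance of each extra draw of 30% in one arm and 50% in the other.

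- All five extra days: spurious difference of about 0.5 to 0.8 points (0.4 at the lowest, depending on the assumed trajectory).
- Extra draws on days 1 and 2 only: 0.35 to 0.82 points.
- Extra draws on days 6 and 7 only: at most about 0.1 point.

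Against the room: 0.5 / 1.31 = 38% and 0.8 / 1.31 = 61%.

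**4. A second route.** Let s be the share of events detectable only through off-schedule values and r the relative difference between arms in detecting them. Both are assumptions.

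- Type I error: true rates 15% (liberal) and 18.5% (restrictive), with the restrictive rate observed as 18.5% × (1 − s·r).
- Power: both true rates 15%, with the restrictive rate observed as 15% × (1 + s·r).
- Probability of declaring noninferiority = Φ[(0.035 − observed difference)/SE − 1.96], with 2037 per arm.

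| s | r | Shift at 15% (15 × s × r, points) | One-sided type I error | Power |
|---|---|---|---|---|
| 0 | any | 0 | 0.025 | 87.9% |
| 2% | 10% | 0.03 | 0.027 | 87.3% |
| 2% | 25% | 0.075 | 0.030 | 86.4% |
| 5% | 25% | 0.19 | 0.039 | 84.0% |
| 10% | 25% | 0.375 | 0.059 | 79.4% |

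Example for s = 5%, r = 25%: observed restrictive rate 18.27%, difference 3.27 points, SE 1.166 points, so Φ(0.231/1.166 − 1.96) = Φ(−1.76) = 0.039.

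**The case against.** The strongest reply has five parts.

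- **The plan does not rest on the schedule alone.** It says only that bias should be minimal, in a limitations section, and elsewhere plans a by-arm comparison of measurement number and days. A reader might infer that the plan claims the schedule prevents bias; it does not. What stands is that the reason given in that sentence is incomplete.
- **Late days are answered by the article's own evidence.** The gap between funded sampling to day 5 and an outcome running to day 7 makes it tempting to see days 6 and 7 as the main problem. The cited cohort has all its listed events by day 3, and the simulation agrees that those days add little. This part stands in full.
- **The imbalance is assumed.** Nothing in the article suggests a 20-point gap in extra testing, and it describes creatinine testing as near universal in perioperative care. This stands as a limit on the magnitude. The equal-frequency precedent is weaker support here: that trial compared pump use, whereas here the arms differ in the hemoglobin level that triggers action, so different blood-sampling patterns are plausible.
- **Use of the routine-care values is inferred.** The article says they are recorded, not that they count. Since a 7-day outcome is defined without restriction to scheduled values, counting them is the natural reading.
- **A sensitivity analysis may sit in the analysis plan, which is not shown.** Its absence from an article would not be a finding on its own. The point is that the article gives a reason for minimal bias that does not cover the outcome as it appears to be ascertained.

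**Conclusion.** The concern holds as a modest robustness gap. A common schedule cannot equalise draws outside it, those draws are ordered by unblinded staff, and the planned count comparison cannot say whether the noninferiority conclusion survives unequal testing. The exposure lies mainly in the first 48 hours.

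The size of about 0.5 to 0.8 points against about 1.3 points of room is an illustration. It depends on an assumed 30% versus 50% chance of each extra draw and on assumed trajectories and noise. If testing is balanced, the effect is zero. Even the upper figure is smaller than the room, so it would not by itself overturn a result centred on no difference.

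A reader might infer that the primary result is biased, or biased toward noninferiority. The article supports neither: it gives no draw frequencies by arm, and the direction could go either way.

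**What to change.** - Prespecify one supporting analysis of the primary outcome using a single creatinine value per scheduled day (days 1, 2, 3 and 5), chosen by a fixed rule that is identical in both arms, for example the first value of the day. The single-value rule is essential: restricting to scheduled days without it would keep the repeat draws on days 1 and 2, which produce most of the illustrated difference.
- Report whether the noninferiority conclusion from this analysis agrees with the primary one, beside the planned comparison of measurement number and days.
- Reword the sentence under Recognized Limitations so that the expectation of minimal bias rests on this analysis and the by-arm comparison, not on the schedule alone. State there, or in the outcome definition, whether routine-care values count.

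The cost is one more analysis of dated values already in the database, with slightly fewer detected events in that analysis. No new data or patients are needed. The article states that no between-group outcome analysis had yet been done, so at that point the addition could still be truly prespecified.

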## Conclusions

Acute kidney injury is a common and important complication of cardiac surgery. The TRICS-III kidney substudy will efficiently and reliably assess the renal effects of a restrictive versus liberal approach to red blood cell transfusion in the presence of acute anemia. It will also assess whether the effects of these approaches differ in patients with and without preexisting chronic kidney disease. Finally, this trial will provide some insights on the interplay between acute anemia, transfusions, and the risk of acute kidney injury.
